## Abstract

Chronic spontaneous urticaria (CSU) is a common dermatologic disease that seriously affects patient quality of life. The choice of therapy to control the disease and prevent its recurrence has always presented a difficult clinical issue. Previous studies have shown that traditional Chinese medicine is a safe and effective treatment for CSU. Recently, the temporal rhythms of CSU, a disease characterized by intermittent flares of active disease and periods of little or no disease, have attracted the attention of traditional Chinese medicine researchers. We designed a multicenter, randomized, controlled study to evaluate the efficacy and safety of combining a Chinese herbal formulation with acupuncture using shu-stream acupoints applied on the corresponding time meridians during disease exacerbations. We plan to recruit 111 outpatients with CSU aged 18 to 65 years. Participants will be randomized to 1 of the 3 groups: group A, which will be given basic acupuncture and the herbal formulation dangui yinzi; group B, which will be given danggui yinzi and shu-stream acupuncture; and a control group, which will be given danggui yinzi alone. Patients will be treated for 4 weeks and followed for 8 additional weeks. Investigators will evaluate the following parameters: the symptoms and side effects of treatment, quality of life (using the chronic urticaria quality of life questionnaire), and overall patient condition. Each week, patients will also complete the measurement of 7-day urticarial activity score. This is the first use of a combination of shu-stream acupoints and Chinese herbal medicine in the treatment of CSU. If successful, it will prove to be a simple, inexpensive, treatment strategy for solving a difficult clinical problem.

## Introduction

1

Chronic spontaneous urticaria (CSU) is an intractable skin disease characterized by intense itching, wheals, and/or angioedema. The disease is defined as having continuous or intermittent symptoms for more than 6 weeks,^[1,2]^ with no specific, identifiable trigger. CSU can seriously affect the patient's physical and mental health and has been associated with anxiety, depression, insomnia, and metabolic syndrome.^[3]^ Its impact on the quality of life is comparable to the impact of having severe coronary artery disease and even exceeds that associated with respiratory allergies.^[4]^

The prevalence of CSU has been reported to be about 0.5% to 1%,^[5–7]^ with a peak incidence between the ages of 20 and 40 years.^[8]^ Women are affected twice as often as men.^[9]^ The etiology of CSU is difficult to determine, but it has been reported to be related to food, medicine, physical factors, vitamin D deficiency,^[10]^ stress,^[2,11]^ chronic occult infection,^[12]^ and autoimmune diseases. The pathological mechanisms responsible for CSU have not been fully elucidated, but mast cells are key effector cells in CSU pathogenesis, and the activation and degranulation of these cells are still the central link in the pathogenesis of urticaria. Mast cells can be activated by immune and nonimmune mechanisms.^[13]^ At present, it is thought that CSU is rarely mediated by allergen-induced, type I allergic reactions, and that a histamine-independent inflammatory reaction is the basis of antihistamine treatment resistance.^[14,15]^ Indeed, the routine use of second-generation H1 antihistamines (sgAH) is recommended as the first-line treatment for CSU.^[16]^ However, a number of studies have shown that even if the dose is increased by 4-fold, the efficacy is not satisfactory.^[17]^ Omalizumab has been shown to be effective in treating some refractory urticaria, but its expensive cost cannot be ignored, and there may be long-term adverse effects.^[18,19]^ Currently, there is no effective treatment for all patients; therefore, it is necessary to explore and evaluate new therapies to provide more treatment options for CSU.

Traditional Chinese medicine (TCM) has unique advantages in the treatment of CSU. The classic herbal formulation danggui yinzi has been widely used clinically to treat the TCM diagnosis of blood deficiency and wind dryness, and it has shown definite efficacy and a good safety profile in this application.^[20,21]^ In addition to Chinese herbal medicine, acupuncture is an important part of complementary and alternative medicine, and studies have demonstrated its effectiveness and safety in treating CSU.^[14,22,23]^

Clinically, CSU is characterized by intermittent episodes of active disease (flares) and periods of little or no disease (remission), and both clinical and experimental studies have found that the level of disease activity is affected by temporal rhythms (ie, disease activity is exacerbated at predictable times during a 24-hour period).^[24,25]^ So, we posit a bold hypothesis: whether CSU can be more effectively treated if these temporal rhythms are considered when determining treatment options. Chinese medical literature supports this theory, stating, “If the disease alleviated sometimes and aggravated sometimes, select Shu-Stream Points.”^[26]^ Therefore, our multicenter study will combine an oral Chinese herbal formulation with the application of time-specific, shu-stream acupoints to determine if this approach can effectively relieve the clinical symptoms of urticaria. This will not only serve to expand the compendium of available external TCM treatments, but it will also provide new areas for research into the treatment of urticaria.

## Methods

2

### Study design

2.1

This study is a multicenter, parallel-group, randomized controlled trial (RCT). The protocol was registered on May 3, 2020, in the Chinese Clinical Trial Registry as Clinical Trial No. ChiCTR2000032609. A total of 111 eligible participants will be enrolled and randomly assigned to the control group or 1 of the 2 treatment arms in a ratio of 1:1:1. Figure 1 shows the study registration schedule, interventions, and assessments. Figure 2 is a flow chart of the study.

**Figure 1 F1:**
[figure not shown]
Spirit figure of enrollment, interventions, and assessments. UAS7 = 7-day urticaria activity score, CU-Q2oL = Chronic urticaria quality of life question-naire. ^∗^Auxiliary examination: blood test, kidney and liver function tests, and electrocardiogram.

**Figure 2 F2:**
[figure not shown]
Flow chart of the study design.

### Ethics approval

2.2

The study is in compliance with the Declaration of Helsinki (Edinburgh 2000 version). The study protocol has been approved by the (No. 2020KT-052). The personal data of the subjects will be kept confidential during the whole trial. Participants are completely voluntary to participate in the clinical research. At any stage of the research, they have the right to withdraw unconditionally, and their medical treatment and rights shall not be affected.

### Recruitment

2.3

The participants will be recruited from the public through Chengdu Integrated TCM & Western Medicine Hospital and 3 subcenters, including the Affiliated Hospital of Chengdu University of TCM, The First People's Hospital of Longquanyi District Chengdu, and Xinjin Hospital of TCM. Before signing informed consent forms, participants will be screened first, and be aware of all the details of the clinical trial and the potential risks.

### Sample size calculation

2.4

The following formula was used to estimate the sample size with the ability to perform multiple sample rate comparisons^[27]^: 

According to the estimation of effective rate,^[28–30]^ the maximum and minimum estimated overall rate of TCM in the treatment of CSU are 95% and 60%, respectively. According to the above formula, the sample size for each group is 33. Thus, assuming that 15% of patients are likely to be lost during follow-up, a total number of study samples is determined to be 111 cases.

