### Treatment plan

3.1

The 3 groups of patients, all diagnosed with blood deficiency and wind dryness syndrome according to the relevant TCM diagnosis and treatment guidelines, will take danggui yinzi mixed with about 150 mL of boiling water 3 times a day at 30 minutes after meals. Group A will also be administered with basic acupuncture as determined by a consensus of experts on the treatment of urticaria in TCM^[33]^: acupuncture Quchi (LI 11), Sanyinjiao (SP 6), and Xuehai (SP10). Group B will be administered shu-stream acupoints applied on the vigorous meridians of Qi and blood. According to accepted TCM theory, the shu-stream acupoints will be scheduled for specific times based on predictable, rhythmic disease exacerbations. For example, if CSU is active between 23:00 and 1:00, Zhlinqi (GB41), the shu-stream acupoints of the gallbladder meridian of foot-shaoyang will be applied.

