#### Main efficacy index

3.2.1

Once a week, study participants will complete the measurement of 7-day urticaria activity score, which sums the daily hive count and itch severity recorded over 7 consecutive days.^[34]^ Quality of life will be evaluated using the chronic urticaria quality of life questionnaire.^[35]^

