### Statistical analysis

3.4

Study data will be analyzed by experts from the Statistics Teaching and Research Office of Chengdu University of TCM, using statistical analysis software package SPSS 22.0. All data will be expressed in terms of mean ± standard deviation. If the sample data are distributed normally and the variance is uniform, the Student *t*-test will be used. The paired sample *T*-test will be used for intra-group comparisons, and the independent sample *T*-test will be used for inter-group comparisons. If the variance is not uniform, the approximate *T*-test will be used to compare the mean of the 2 independent samples. If the sample data are not normally distributed, the nonparametric rank sum test will be used. Pearson Chi-squared test will be used to count the data. Statistical significance will be set at *P* < .05.

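### The sample size is derived from an effective rate that is not a listed outcome and a 35-point gap that is tied to no arm, so 33 per group is not justified for UAS7 or CU-Q2oL

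*Protocol article*

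**What the plan says.** - **Sizing (section 2.4).** A formula is used to "estimate the sample size with the ability to perform multiple sample rate comparisons". Its inputs are given as "the maximum and minimum estimated overall rate of TCM in the treatment of CSU are 95% and 60%, respectively". The result is that "the sample size for each group is 33". Then, "assuming that 15% of patients are likely to be lost during follow-up", the total is set: "a total number of study samples is determined to be 111 cases". With 1:1:1 allocation (section 2.1) this is 37 per arm.
- **Main outcomes (section 3.2.1).** "Once a week, study participants will complete the measurement of 7-day urticaria activity score". CU-Q2oL stands under the same heading. Neither is ranked first and no time point is singled out.
- **Secondary outcomes (section 3.2.2).** A TCM symptom score and a visual analogue scale.
- **Treatment (section 3.1).** Patients in all three groups "will take danggui yinzi mixed with about 150 mL of boiling water 3 times a day". Groups A and B add different acupuncture schemes; the control group has the herbs alone.
- **Analysis (section 3.4).** "All data will be expressed in terms of mean ± standard deviation". Groups are compared by independent t-test, or by rank sum test if the data are not normal. Pearson's chi-squared test is mentioned for count data, with no outcome attached.

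**The concern.** A sample size supports a trial's conclusions only if it is worked out for an outcome the trial will analyse and for a difference its arms might plausibly show. Section 2.4 does neither visibly.

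First, it sizes for a proportion, while every listed efficacy outcome is a score. No difference or SD is given for UAS7 or CU-Q2oL.

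Second, the proportions are described as the extremes of the overall TCM rate. A formula for several rates uses the largest and smallest group rates, so their spread becomes the assumed gap between arms. Yet every arm, control included, receives a TCM treatment, and the article does not say which arm is expected to reach 95% and which 60%.

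At stake is how the result is read. A reader of section 2.4 will take the trial as adequately sized for its main outcomes. If a moderate difference exists and the comparison is not significant, that could be taken as no benefit although the trial had about an even chance, or less, of detecting it.

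**Working it through.** **1. The plan's own 33.** The printed formula is lost from the text available, and power is not visible. As an assumption, take the usual arcsine formula for three rates, with alpha 0.05 and 2 degrees of freedom:

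n = 2λ / h², where h = 2·asin√0.95 − 2·asin√0.60 = 2.691 − 1.772 = 0.918.

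| Power | λ | n per group |
|---|---|---|
| 80% | 9.63 | 22.9 |
| 90% | 12.65 | 30.0 |
| 95% | 15.44 | 36.6 |

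Under this formula 33 corresponds to about 93% power. A two-sample formula for proportions gives 34 at 90% power with continuity correction, and 34 at 95% without it. So 33 is plausible but not confirmed. The point does not depend on it: it concerns the inputs and the outcome, not the arithmetic.

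**2. Sizing outcome against listed outcomes.**

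| Section | Quantity | Type |
|---|---|---|
| 2.4 | effective rate | proportion |
| 3.2.1 | UAS7, CU-Q2oL | scores |
| 3.2.2 | TCM symptom score, VAS | scores |

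No cut-off that would turn a score into a response is stated.

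**3. Evaluable patients.** 111/3 = 37 per arm, and 37 × 0.85 = 31.45, so about 31. (Separately, 33/0.85 = 38.8, or 39 per arm and 117 in all, so 111 does not preserve 33 after 15% loss.)

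**4. What 31 per arm can show on a score.** Two-sample comparison of means, in SD units because no SD is given. The normal approximation is d = (z₁₋α/₂ + z_power)·√(2/n), with √(2/31) = 0.254.

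- Alpha 0.05, 80% power: (1.960 + 0.842) × 0.254 = 0.71; with the t distribution, 0.72.
- Alpha 0.05, 90% power: 0.84 with the t distribution.
- Alpha 0.05/3, 80% power: (2.394 + 0.842) × 0.254 = 0.82; with the t distribution, 0.84.

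Power for an assumed 0.5 SD (noncentrality 0.5 × √(31/2) = 1.97) is 49% at alpha 0.05 and 32% at 0.05/3. Even with 33 per arm, 0.5 SD has 52% power and the detectable difference is 0.70 SD (80% power, alpha 0.05). Reaching 80% power for 0.5 SD would take about 64 per arm unadjusted, or 86 adjusted.

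**5. Dependence on the 60%, even on the rate scale.** Top arm 95%, 31 per arm, three-arm arcsine test at alpha 0.05. The lowest-arm values of 70%, 75% and 80% are assumptions. Noncentrality is n·h²/2 with the third arm midway on the arcsine scale (least favourable), and 2n·h²/3 with it equal to one extreme.

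| Lowest arm | Third arm midway | Third arm at an extreme |
|---|---|---|
| 60% (plan) | 91% | 97% |
| 70% | 70% | 83% |
| 75% | 55% | 68% |
| 80% | 37% | 48% |

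**The case against.** The best defence has four parts.

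*A rate may be defined elsewhere.* Section 3.4 provides a chi-squared test, and the TCM symptom score follows a cited guideline that may contain a response category; the full protocol might also define one. That cannot be ruled out. But the article lists its outcomes and none is a rate, and a category derived from the symptom score would be secondary. The main outcomes would still be unsized.

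*The two rates may be arm rates.* A reader might infer that 95% and 60% are certainly not expected arm rates. The text does not go that far. Acupuncture is also part of TCM, so 95% for combined treatment and 60% for herbs alone is not strictly excluded. What stands is that the article does not say so and offers nothing to support that gap.

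*The size is not uninformative.* A reader might conclude that 33 per group says nothing about UAS7. It does imply a detectable difference, as shown above. What is missing is a justification in those terms.

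*No contrast is ranked first.* It is tempting to treat group B against group A as the key comparison, because it isolates the time-specific points. The article states its aim as evaluating acupuncture combined with herbal medicine and names no leading contrast, so the figures here apply to any pair of arms. Likewise, UAS7 is not the sole main outcome, and no primary week is set.

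The discussion also concedes that further evaluation will be needed whatever the results. That softens the risk of a non-significant result being over-read, but does not repair section 2.4.

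**Conclusion.** The concern holds as a mismatch between stated sections, not as missing detail. Section 2.4 sizes the trial on a quantity that sections 3.2.1 and 3.2.2 do not list, with a gap that the shared herbal treatment gives no reason to expect and that is linked to no arm. For the main outcomes, 111 patients support only large pairwise differences: about 0.72 SD unadjusted, or 0.84 SD with alpha divided by three, at 80% power.

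These figures assume two-sided testing, approximately normal scores, 31 evaluable per arm and no adjustment for baseline. The 0.5 SD is illustrative. The article does not support any claim that 33 is miscalculated, or that a particular larger sample size is required, since no UAS7 or CU-Q2oL difference or SD is given. It should be fixed, but it is a defect of justification and does not call for a change in enrolment.

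**What to change.** Keep 111 and rewrite section 2.4:

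1. Name one primary outcome (UAS7 or CU-Q2oL) and one time point, and say which pairwise comparisons are planned and whether alpha is shared among them.
2. Replace the 95%/60% rationale with the detectable difference. For example: with 37 randomised per arm and 15% loss (about 31 evaluable), the trial has 80% power for a pairwise difference of about 0.72 SD at two-sided 5%, or about 0.84 SD if alpha is divided over three comparisons. Convert this to score points with a stated and sourced SD.
3. State that pairwise differences will be reported with confidence intervals, and that a non-significant result will not be read as no benefit.

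If an effective rate is in fact intended as an outcome, define it, list it in section 3.2 and say which arm each assumed rate belongs to. The main scores still need the statement in item 2.

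The cost is a rewritten section and a choice of primary outcome, with no added patients. The downside is that the stated capability becomes less favourable.

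### Minor arithmetic error in section 2.4: from 33 per group and 15% loss the total is 117, not 111, and 111 covers a loss of only about 10.8%

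*Protocol article*

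**What the plan says.** The sample size is set out in the protocol article, section 2.4 (Sample size calculation). It takes as inputs that "the maximum and minimum estimated overall rate of TCM in the treatment of CSU are 95% and 60%, respectively", and reports that "the sample size for each group is 33". The allowance for loss follows directly: "assuming that 15% of patients are likely to be lost during follow-up, a total number of study samples is determined to be 111 cases".

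Section 2.1 (Study design) repeats the total, "A total of 111 eligible participants will be enrolled and randomly assigned", and fixes the allocation, with patients "randomly assigned to the control group or 1 of the 2 treatment arms in a ratio of 1:1:1". The total of 111 therefore means 37 per group. The abstract gives 111 as well. The article states no other loss rate and no other required number.

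**The concern.** The 33, the 15% and the 111 stand together in one short paragraph, and the total is presented as following from the other two. It does not. An allowance for loss should leave the required number in place after the assumed fraction has gone, and 111 does not do that at 15%.

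What is at stake is the accuracy of a headline design figure. A reader is told that the trial can lose 15% of its patients and still hold the number it was sized for. On the plan's own inputs it can lose about 10.8%. No other allowance for attrition is visible, and section 2.7.3 (Termination and withdrawal criteria) removes patients for several reasons besides loss to follow-up, so the article shows no spare margin that would make up the difference.

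**Working it through.** **Inputs, all from the protocol article**
- Required per group before loss: 33 (section 2.4), so 3 × 33 = 99 in total.
- Assumed loss: 15% (section 2.4).
- Stated total: 111 (section 2.4, section 2.1, abstract).
- Allocation: three groups, 1:1:1 (section 2.1), so 111/3 = 37 per group.

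**Reproducing the stated figure**
- Multiplying by one plus the loss rate: 33 × 1.15 = 37.95.
- Dropping the fraction gives 37, and 37 × 3 = 111. This matches, but the route is inferred; the article does not describe the step.
- Rounding 37.95 up, as is usual for a sample size, gives 38 per group and 114 in total. The same shortcut on the total gives 99 × 1.15 = 113.85, also 114.
- The inflation actually applied is 111/99 − 1 = 12.1%.

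**The correct inflation**
- Required number divided by the fraction retained: n/(1 − d) = 33/0.85 = 38.8, so 39 per group and 117 in total.
- From the total: 99/0.85 = 116.5, also 117.
- Check: 39 × 0.85 = 33.15 per group, which meets 33.
- 117 − 111 = 6 patients, or 6/111 = 5.4% of the stated total.

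**What 111 delivers**
- At 15% loss: 111 × 0.85 = 94.35 in total, or 37 × 0.85 = 31.45 per group.
- Shortfall: 99 − 94.35 = 4.65 in total, or 33 − 31.45 = 1.55 per group, about 5%.
- Largest loss that still leaves 99: (111 − 99)/111 = 12/111 = 10.8%.

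**Size of the effect on power (assumption)**

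The formula in section 2.4 is not visible and the text shown states no power. As an assumption, take the usual arcsine formula for comparing three rates: a chi-squared test with 2 degrees of freedom at the 5% level and noncentrality n(2·arcsin√0.95 − 2·arcsin√0.60)²/2.

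| Patients per group | Power under this assumption |
|---|---|
| 33 | 92.7% |
| 31.45 | 91.4% |
| 31 | 91.0% |

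The loss is 92.7 − 91.4 = 1.3 points at 31.45 per group and 92.7 − 91.0 = 1.7 points at 31. Under the same formula, 90% power needs 30 per group.

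**The case against.** **The error is too small to matter.** The gap is about 1.5 patients per group. Under the assumed formula the trial stays above 90% power at 31 per group, and no analysis or conclusion depends on the difference. This stands, and it is why the point is minor. It does not make the stated allowance correct.

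**The 33 may be a rounded figure.** If the formula gave a value just above 32 that was reported as 33, the shortcut would reach 37 without rounding down: 32.01 × 1.15 = 36.8, so 37. That is possible, since the unrounded result cannot be seen. It still relies on the wrong inflation: even 32.01/0.85 = 37.7 rounds up to 38 per group, or 114. No reading of the stated figures gives 111 under division by 0.85.

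**Patients who are lost may still be analysed.** The abstract describes 4 weeks of treatment and 8 further weeks of follow-up, with weekly activity scores, and the article does not fix the time point of the main comparison. Someone lost after week 4 could contribute end-of-treatment data. So 31 per group is the number left at the end if loss reaches 15%, not necessarily the number in every analysis. This stands as a limit on the consequence. It does not rescue the 111, because the plan's own allowance treats lost patients as needing replacement.

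**An article condenses a fuller protocol.** True, but the point concerns no omission. All the figures needed are printed, and they disagree with each other.

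**Conclusion.** The total in section 2.4 is wrong on the plan's own inputs. With 33 per group and 15% loss it should be 117, and the stated 111 covers up to about 10.8%. This rests only on the printed 33, 15%, 111 and 1:1:1 ratio, and is independent of the missing formula.

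It is a minor error. At 15% loss the shortfall is about 1.5 patients per group. The estimate of 1 to 2 points of power depends on the assumed arcsine formula and should be read only as an indication of scale.

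A reader might infer that the trial is underpowered or that it must recruit more patients. The documents support neither. No power is visible against which to call the trial short, and under the assumed formula it remains above 90%. Nor can it be said that the 33 itself is wrong: without the formula and the intended power, it can only be taken as given.

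**What to change.** In section 2.4, keep 111 and correct the allowance. State that 111 (37 per group) leaves the required 33 per group if loss is no more than about 10.8%, and that a loss of 15% would leave about 31 per group. If the full protocol gives a power or detectable difference, restate it at about 31 per group. Section 2.1 and the abstract give only the total and need no change. The cost is wording in one paragraph.

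Only if the sponsor chooses to keep the 15% allowance should the total change: 39 per group and 117 in section 2.4, with 117 carried into section 2.1 and the abstract. The cost is six more patients.
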